### Study design

The Fraction study is an ongoing prospective multicenter cohort, coordinated by the CHU of Toulouse, (https://clinicaltrials.gov/ct2/show/NCT02806154) which evaluates the discriminant ability of ALM measured by DXA to predict the incidence of severe chemo-toxicity in older adults with cancer treated with first line chemotherapy for solid neoplasm or lymphoma.

### Participants

Eligible patients are above 70 years of age and are diagnosed with solid neoplasms (breast, prostate, bladder, colo-rectal, ovarian cancers) or lymphomas at a locally advanced or metastatic stage treated for first-line chemotherapy with a life expectancy above 3 months.

Patients treated by a combination of chemotherapy with targeted therapies or radiotherapy were excluded due to the potential difficulty to measure the isolated effects of chemotherapy.

Patients whose weight exceeds 136 kg and height is above 196 cm are excluded because it is the limit for the DXA table and may induce errors in assessing body composition, injury to the patient and damage to the DXA table.

Other hemopathies than lymphoma were excluded because their potential treatments vary and they have various toxicity responses.

Cognitive status was evaluated with Mini-Mental Status Examination (MMSE) and the cut off score of 20 was chosen to exclude certain participants due to difficulty of follow-up, providing informed consent and safety concerns. Moreover, patients under protection measures are excluded for the same reasons.

Inclusion and exclusion criteria are summarized in Table 1.

**Table 1 Tab1:** Fraction study inclusion and exclusion criteria

Inclusion criteria: 1. Age ≥ 70 years old 2. Cancer types: Breast, prostate, bladder, colo-rectal, ovarian cancers, and lymphoma - Metastatic or locally advanced neoplasm 3. First-line chemotherapy 4. Performance status World Health Organization (WHO) score 0 to 3 5. Capacity to give a written informed consent 6. Life expectancy > 3 months Exclusion criteria: 1. Targeted therapies in combination with chemotherapy 2. Radiotherapy in combination with chemotherapy 3. Height > 196 cm and weight > 136 kg (DXA not feasible) 4. Hemopathy excluding lymphoma 5. Cognitive impairment (MMSE < 20/30) due to difficulty of follow-up and providing informed consent	

Recruitment will be performed by four geriatric oncology units: Midi-Pyrénées; Provence Alpes Côte d’Azur, Pays de la Loire and Languedoc Roussillon (Toulouse University hospital, Claudius Regaud institute of Toulouse, Nice University hospital, Nantes University hospital and the Val Aurel institute of Montpellier).

Participants will be recruited over 3 years, beginning in March 2017. The study goal is to recruit 160 participants over a two-year period.

A team comprising an oncologist and geriatrician was chosen in each recruitment center to verify protocol compliance. Patients will be referred to these units by their oncologist, hematologist, onco-geriatrician or geriatrician. The study protocol was reviewed and approved by the Committee for the protection of persons of the southwest and overseas region III for all sites. All patients will sign the informed consent form prior to the study.

A screening visit will be conducted within a month before the baseline visit by a study coordinator to verify eligibility criteria and protocol aspects will be discussed with the patient.

Once the patient’s informed consent has been obtained a baseline visit will be scheduled.

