### Statistical analysis

#### Sample size calculation and primary analysis

The primary objective of our study is to evaluate the discriminant ability of ALM to predict severe toxicity or chemotherapy interruption due to unacceptable toxicity. Discriminant ability will be evaluated by calculating the area under the receiver operation characteristic (ROC) curve (AUC). Incidence above grade > 2 toxicity occurs in about 50% of the elderly treated with chemotherapy [8]. Supposing a toxicity rate of 50%, 160 patients were required to estimate a 95% confidence interval of an AUC equal to 75% with an accuracy of +/− 7.5% [29].

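### The DXA exclusion joins the weight and height limits with *and*, so as written it contradicts its own reason for any patient over exactly one limit (minor wording error)

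*Protocol article*

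**What the plan says.** The rule appears twice in the protocol article, both times under Participants.

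- Running text: "Patients whose weight exceeds 136 kg and height is above 196 cm are excluded because it is the limit for the DXA table". The sentence goes on to say that this "may induce errors in assessing body composition, injury to the patient and damage to the DXA table".
- Table 1, exclusion criterion 3: "Height > 196 cm and weight > 136 kg (DXA not feasible" (the bracket closes there).

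The order of the two measurements is reversed between text and table, but the connective is the same. Nothing elsewhere in the article says that exceeding one limit is enough.

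DXA supplies the primary predictor. Under Study design, the study "evaluates the discriminant ability of ALM measured by DXA to predict the incidence of severe chemo-toxicity". Under Study scheme, the scan is part of the baseline visit. Eligibility is verified beforehand, at a screening visit held by a study coordinator.

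**The concern.** A table has a weight limit and a length limit, and a patient can breach either without the other. The protocol's reason for excluding patients is engaged as soon as one limit is passed. The written rule acts only when both are passed.

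The eligibility rule and its justification therefore select different groups. The patients on whom they differ are those over one limit only, whom the justification describes as at possible risk of injury or of an erroneous body-composition reading. If a centre applied the wording literally, such a patient could be enrolled. The centre would then face a scan outside the equipment limit, or a participant whose appendicular lean mass (ALM) may be unreliable or unavailable. Several centres recruit, so a rule that depends on each reader mentally correcting it may also be applied inconsistently.

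**Working it through.** **1. The rule against its reason.** Inputs are the two limits (136 kg, 196 cm) from the Participants text and Table 1. The heights and weights below are chosen only to fill the four possible cells.

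| Height | Weight | Over height limit | Over weight limit | Excluded as written (both) | Excluded by the stated reason (either) |
|---|---|---|---|---|---|
| 190 cm | 120 kg | no | no | no | no |
| 190 cm | 140 kg | no | yes | **no** | **yes** |
| 200 cm | 120 kg | yes | no | **no** | **yes** |
| 200 cm | 140 kg | yes | yes | yes | yes |

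The two readings agree when neither or both limits are exceeded. They disagree in the two middle rows, that is, for every patient over exactly one limit.

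For scale, 136 kg at 170 cm is a BMI of 136 / 1.70² = 47.1. A patient of that height who is slightly heavier is over the weight limit and not excluded by the literal rule.

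**2. How Table 1 writes alternatives.** Where either of two related conditions is enough to exclude, the table numbers them separately: "1. Targeted therapies in combination with chemotherapy 2. Radiotherapy in combination with chemotherapy". Height and weight instead share one number and are joined by *and*. By the table's own layout, criterion 3 reads as a single joint condition.

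**3. Does it touch the sample size?** Under Sample size calculation and primary analysis, "160 patients were required to estimate a 95% confidence interval of an AUC equal to 75% with an accuracy of +/− 7.5" percentage points, supposing a 50% toxicity rate. I reproduced this with the Hanley–McNeil variance, with A = 0.75 and n₁ = n₂ = 80:

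- Q₁ = A/(2 − A) = 0.75/1.25 = 0.6000
- Q₂ = 2A²/(1 + A) = 1.125/1.75 = 0.6429
- Variance = [A(1 − A) + (n₁ − 1)(Q₁ − A²) + (n₂ − 1)(Q₂ − A²)] / (n₁n₂) = [0.1875 + 79 × 0.0375 + 79 × 0.0804] / 6400 = 9.498/6400 = 0.001484
- Half-width = 1.96 × √0.001484 = 0.0755

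This agrees with the stated 7.5 points to rounding, so the plan's figure is reproduced.

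The article does not say how many patients exceed one limit. As an assumed range, suppose that 2 or 8 of the 160 had no usable scan, split evenly between events and non-events:

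| Usable scans | Half-width | Change from 160 |
|---|---|---|
| 160 | 0.0755 | none |
| 158 | 0.0760 | 0.05 points |
| 152 | 0.0775 | 0.2 points |

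The upper value (5% of the sample) is an illustration with no source in the article. Even there the change is small.

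**The case against.** The best defence is that the intent can be read on the page. Table 1 labels the criterion as a matter of scan feasibility, and the text ties it to the table's limit. A coordinator who reads criterion and label together would probably turn away a patient over either limit. The sentence can also be read distributively, as covering patients over 136 kg and, separately, patients over 196 cm. The article describes qualified technicians, a screening visit and a team at each centre to verify compliance. It also condenses a fuller protocol that is not shown, whose operative criterion may be worded differently.

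Most of this stands. It makes a drafting slip much more likely than a deliberate choice, and it makes actual harm remote. It does not remove the inconsistency: both statements carry the same conjunction, the table lists alternatives separately elsewhere, and no other sentence settles the matter.

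A reader might also infer more than the article supports:

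- **That a patient over one limit would have to be scanned.** Nothing compels this. The text only fails to exclude the patient.
- **That ALM would be invalid or missing for such patients.** The article says only that errors may arise.
- **That the criterion as written excludes practically nobody.** This needs a height and weight distribution, which is not given.

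**Conclusion.** The point holds as a minor error of wording. As written, the criterion contradicts its own rationale for any patient over exactly one of the two limits, in both places where it is stated. It is probably a drafting error. That it affects few patients is an assumption about people aged 70 or over, since the article gives no data on height or weight.

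A reader might take this as a threat to the primary analysis or as a serious safety defect. The article supports neither. The target of 160 is unaffected, and AUC precision moves by at most 0.2 points over the range assumed above. A safety consequence would require staff to disregard both the equipment limit and the criterion's own label. The point is still worth correcting, because this is an operative eligibility rule and it governs the measurement that yields the primary predictor.

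**What to change.** Reconcile the criterion with its stated reason in the Participants text and in Table 1, exclusion criterion 3. Keep the numeric limits and change the connective, so that the rule reads: height > 196 cm or weight > 136 kg. Splitting it into two numbered criteria would do the same job and match the way the table treats targeted therapy and radiotherapy.

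Then check that the full protocol and any eligibility checklist or electronic form use the same logic. The article does not show that logic, so it may already be right.

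The cost is one word in two places plus that check. No sample-size or analysis figure needs recalculating.

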### Data collection

Patient related information age, gender, socio-economic status and education, social support and medication are recorded.

#### DXA parameters

Measurement of body composition parameters by dual energy X-ray absorptiometry DXA, LUNAR iDXA GE, and HOLOGIC was performed by qualified technicians and cross calibration was done in between centers.

Indeed, the DXA machine was used to target a specific region of interest; appendicular lean mass, and underwent further calibration procedures due to the fact that two systems were used Hologic system© and the Lunar system© (iDXA, General Electrics). To limit result variability due to the use of different DXA machines and softwares, calibration was done using the same phantom following a standardized procedure.

Total and regional distribution of lean mass, bone mass and fat mass was estimated. Appendicular lean mass and fat mass were standardized using evidence-based international criteria.

#### Cancer characteristics and previous treatment

Tumor-specific variables included WHO performance status, primary tumor location (histologic grade, TNM classification …) and proposed cancer treatment strategies are recorded.

#### Geriatric assessment

The patient evaluation assisted by a health care team member consisted of measures of comorbidity using the score cumulative illness rating scale geriatric (CIRS-G) [21], psychological state with the geriatric depression scale (GDS 15) [22], functional autonomy Katz’s Activities of daily living (ADL) [23], Lawton’s instrumental activities of daily living (IADL) [17] and quality of life assessed by EORTC QLQC 30 [19]. The nutritional status was evaluated by loss of weight as a percentage, Mini Nutritional Assessment (MNA) [24] and Body Mass Index (BMI) defined by weigh devised by height square. Physical performance was assessed using the Short Physical Performance Battery SPPB [18] a composite score of chair stand, walking speed and balance test.

The physicians then performed a clinical examination, a cognitive assessment with the Mini Mental State Examination (MMSE) [25] and completed series of oncological risk scores: the G8 score [20], the cancer and aging research group CARG score [8] and the chemotherapy risk assessment scale for high CRASH [7].

Pretreatment laboratory data including complete blood counts (white blood cell, neutrophil, lymphocyte, platelet values), albumin, creatinine, C-reactive Protein (CRP) and lactate dehydrogenase (LDH) were recorded before first-line chemotherapy was administered.

#### Chemotherapy toxicity

Chemotherapy toxicity (hematological and non-hematological toxicity) is assessed at each chemotherapy cycle during scheduled or emergency visits with the patient’s oncologist according to their cancer plan within the one-year follow-up according to the national cancer institute common terminology criteria for adverse events (NCI CTCAE), version 3.0 [16] based on questioning, physical examination, and laboratory tests. Toxicity is graded as mild (Grade 1), moderate (Grade 2), severe (Grade 3), life-threatening (Grade 4) or fatal (Grade 5). The principal investigator and site sub-investigator will review patient’s chemotherapy course to confirm any Grade 3 to 5 declared chemotherapy-related toxicity.

In order to compare different chemotherapy protocols, the MAX 2 index will be used to estimate the average per patient risk for chemotherapy toxicity. This procedure has been previously used in research [7].

Treatment benefits is regularly assessed by the oncologist and is classified using the Response Evaluation Criteria in Solid Tumors (RECIST 1.1) [26] for solid neoplasms, or by the revised Cheson criteria for lymphomas [27]. Treatment will be interrupted in case of disease progression or unacceptable toxicity as per the oncologist’s discretion.

### Study scheme

Baseline visit (including DXA assessment) is organized in a day care hospital unit where a geriatrician and a nurse will conduct the previous extensive comprehensive geriatric assessment.

Patient’s follow-up will be pursued according to their cancer care plan by their oncologist. Visit frequency depends on the cancer type and the treatment plan. The oncologist will perform a clinical examination and record chemotherapy toxicity according to the WHO toxicity grading system at each visit [16].

Participants are asked to return for simplified follow-up geriatric assessments within the first 3 months, 6 months and a year after inclusion. At this visit, a nurse trained in onco-geriatrics will perform during the visit measures of functional status (ADL, IADL) [17], nutrition (weight, MNA [28], BMI), physical performance (SPPB) [18] and the European organization for research and treatment of cancer quality of life score (QLQC-30) [19]. (Fig. 1).

**Fig. 1 Fig1:**
[figure not shown]
Assessment and follow up study scheme

Survival data will be collected for all patients during the study period.

### Statistical analysis

#### Sample size calculation and primary analysis

The primary objective of our study is to evaluate the discriminant ability of ALM to predict severe toxicity or chemotherapy interruption due to unacceptable toxicity. Discriminant ability will be evaluated by calculating the area under the receiver operation characteristic (ROC) curve (AUC). Incidence above grade > 2 toxicity occurs in about 50% of the elderly treated with chemotherapy [8]. Supposing a toxicity rate of 50%, 160 patients were required to estimate a 95% confidence interval of an AUC equal to 75% with an accuracy of +/− 7.5% [29].

#### Secondary endpoint analysis

Secondary objectives, which correspond to the evaluation of discriminant ability, will be evaluated using similar methodology as used in the primary endpoint.

To determine a toxicity model associated with the occurrence of severe toxicity, the population will be partitioned into two cohorts, a training cohort (first 100 patients recruited) and a validation cohort (last 60 patients recruited). This allows a temporal validation which can be considered an intermediate between internal and external validation. In the training cohort, a penalized logistic regression model with elastic net regularization [30] via the lasso will be used to identify associations between severe toxicities and different parameters (body composition, geriatric assessment parameters …) [31]. A 10-fold cross validation will be performed to select the best penalty lambda parameter. The other parameter of the Elastic net method, the mixing parameter α, will be set to a default value of 0.5 [32]. Using a resampling approach, bootstrap selection stability (BSS) will be computed for each parameter. Only parameters with high BSS will be selected in the final model. Based on the linear predictor given by the model, a classifier predicting severe toxicity will be computed. The risk group will be defined by dichotomizing the toxicity profile using the area under the ROC curve and will be estimated with corresponding 95% confidence interval (Hanley method) [33]. Risk group will be then applied on the validation cohort. Sensitivity and specificity of the toxicity risk group will be evaluated and compared to other published tools (CRASH [7], CARG [8], G8 [20]). All statistical analyses will be performed by using Stata v13.0 or R software.

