## Methods/design

### Objectives of the study

The principal objective is to evaluate the ability of ALM (measured by dual-energy X-ray absorptiometry (DXA)) to predict the incidence of severe toxicity grade 4 hematologic or grade 3 to 4 non hematologic toxicity (as defined by the National Cancer Institute-Common Toxicity Criteria (NCI-CTC version 3)) [16] and/or chemotherapy interruption related to unacceptable toxicity in older cancer-patients treated with first-line chemotherapy for solid neoplasm or lymphoma.

The following are the secondary objectives:

To evaluate various other body composition parameters: total lean mass, total fat mass, ALM standardized by squared height or body mass index (ALM / height^2^, ALM / BMI), an index of ALM / appendicular fat mass, total lean mass index (total lean mass/ height^2^), total fat mass index (total fat mass / height^2^) in predicting toxicity. These parameters, will then be studied to assess their ability to predict functional decline (defined as a loss of ≥0.5 points in ADL score [17] during follow-up), physical performance decline (defined as a loss ≥1 point in the SPPB [18] during follow-up), quality of life decline (defined as a loss ≥10 points in the EORTC QLQ-C30 questionnaire [19] during follow-up) and early death (defined as death within the 3 first months of the first-line of chemotherapy).

Moreover, a toxicity risk profile will be studied by using combined scores including parameters of body composition and a geriatric assessment. This toxicity profile will be compared to current existing toxicity scores such as the CRASH score [7], CARG [8] and the G8 [20].

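### The AUC cannot by itself set the risk-group cut-off, and sensitivity and specificity without a common operating point do not show which tool discriminates better

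*Protocol article*

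**What the plan says.** All of this is in the protocol article.

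- **Objectives of the study.** A combined profile of body composition and geriatric assessment is to be set against published scores: "This toxicity profile will be compared to current existing toxicity scores such as the CRASH score", and likewise CARG and G8.
- **Sample size calculation and primary analysis.** Discriminant ability is measured by the AUC.
- **Secondary endpoint analysis, opening sentence.** "Secondary objectives, which correspond to the evaluation of discriminant ability, will be evaluated using similar methodology as used in the primary endpoint".
- **Same section, model building.** An elastic net is fitted in the first 100 patients, with a bootstrap stability filter on the candidate parameters. The classifier comes from the linear predictor.
- **Same section, cut-off.** "The risk group will be defined by dichotomizing the toxicity profile using the area under the ROC curve". The same sentence goes on to attach a 95% confidence interval by the Hanley method.
- **Same section, validation and comparison.** "Risk group will be then applied on the validation cohort", which is the last 60 patients. Then: "Sensitivity and specificity of the toxicity risk group will be evaluated and compared to other published tools", namely CRASH, CARG and G8.

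The article gives no threshold criterion, no cut-offs for the three published tools and no rule for matching them.

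**The concern.** There are two difficulties.

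First, the sentence that defines the risk group names a quantity that does not determine a cut-off. It then attaches an interval method that belongs to an AUC, not to a cut-off or a group. Two steps seem to have been run together: estimating the AUC of the profile, and choosing where to cut it. Someone following the text would have to supply the criterion, and could do so after seeing the data.

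Second, the aim is to compare discrimination, but the comparison named uses sensitivity and specificity. These depend on where each tool is cut as well as on how well it ranks patients. Without a common operating point, two tools with the same discrimination can give quite different pairs. A statement that the new profile does better than CRASH, CARG or G8 could then reflect the cut-offs alone.

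**Working it through.** **Inputs.** From Sample size calculation and primary analysis: AUC 0.75, toxicity rate 50%, N = 160, half-width 0.075. From Secondary endpoint analysis: 100 training and 60 validation patients. Assumed here, because the documents give no score distributions: equal-variance binormal scores.

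**1. The plan's own figure.** Hanley variance of an AUC A with n1 events and n2 non-events:

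SE² = [A(1−A) + (n1−1)(Q₁−A²) + (n2−1)(Q₂−A²)] / (n1·n2), with Q₁ = A/(2−A) and Q₂ = 2A²/(1+A).

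For A = 0.75: Q₁ = 0.600, Q₂ = 0.643, A² = 0.5625. With 80 and 80: SE² = [0.1875 + 79 × 0.0375 + 79 × 0.0804]/6400 = 0.00148, SE = 0.0385, half-width 1.96 × 0.0385 = 0.0755. The 160 patients are reproduced to rounding. The sample size is not in question.

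**2. One AUC, many operating points.** The separation is d = √2 × z(0.75) = 1.414 × 0.6745 = 0.954. At a cut-off c, specificity = Φ(c) and sensitivity = Φ(d − c).

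| Cut-off c | Sensitivity | Specificity | (Sens + spec)/2 |
|---|---|---|---|
| 0 | 0.830 | 0.500 | 0.665 |
| 0.238 | 0.763 | 0.594 | 0.679 |
| 0.477 | 0.683 | 0.683 | 0.683 |
| 0.715 | 0.594 | 0.763 | 0.679 |
| 0.842 | 0.545 | 0.800 | 0.672 |
| 0.954 | 0.500 | 0.830 | 0.665 |

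Every row has the same AUC of 0.75, so that AUC cannot say which row to use.

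**3. The reading that does give a cut-off.** A dichotomised score has its own AUC, equal to (sensitivity + specificity)/2. Maximising it is the same as maximising the Youden index, sensitivity + specificity − 1. In the table this picks c = 0.477. That is a usable rule, but it is not the one written.

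**4. What the cut-off alone can do to a comparison.** Take two tools, both with AUC 0.75, one cut at 50% specificity and the other at 80%. Sensitivity is 83.0% against 54.5%, a difference of 28.5 points. Specificity differs by 30 points the other way. The mean of the two hardly moves (0.665 against 0.672).

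**5. Precision in the validation cohort.** At 50% toxicity, 60 patients give 30 events and 30 non-events.

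- Single AUC of 0.75: SE² = [0.1875 + 29 × 0.0375 + 29 × 0.0804]/900 = 0.00401, SE = 0.0633, half-width 0.124.
- Paired difference of two such AUCs: half-width = 1.96 × 0.0633 × √[2(1−r)], where r is the correlation between the two AUC estimates. The documents do not give r. For r = 0, 0.5 and 0.8 the half-width is 0.175, 0.124 and 0.078.
- Single sensitivity or specificity on 30 patients: 1.96 × √[p(1−p)/30], which is 0.18 at p = 0.5 and 0.14 at p = 0.8.

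**The case against.** **The rule can be executed.** A reader might infer that no cut-off can be obtained at all. That goes too far: under the Youden reading in step 3 the sentence works. What stands is that the reader has to supply that reading. An unshown analysis plan may name the criterion, but the article does not merely leave it out. It states one that, as worded, selects nothing.

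**Unmatched cut-offs are not stated.** A reader might infer that the plan uses each published tool at its own cut-off. The article does not say so. It is silent on operating points, and a condensed article may leave them to the full plan. What stands is narrower: no common operating point is named in the one comparison described.

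**An AUC comparison is not excluded.** The opening sentence of Secondary endpoint analysis carries the primary methodology over to the secondary objectives, so an AUC for each tool may be intended. But the sentence dealing with the published tools names only sensitivity and specificity.

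**Both measures are reported.** A reader who sees 83%/50% beside 54%/80% would see a trade-off, not a winner. That is fair, and the sensitivity gap should not be quoted alone. It also confirms that the pair does not settle which tool discriminates better. As a description of clinical classification at pre-stated cut-offs, sensitivity and specificity remain legitimate.

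**Optimism.** Because the Hanley interval is mentioned before the validation step, a reader might infer that an over-optimistic training AUC will be presented as the model's performance. That rests on sentence order alone. The plan holds out 60 patients and applies the risk group to them before the comparison. Labelling the estimates clearly is enough.

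**Conclusion.** The point holds in a limited form. The threshold criterion for the risk group is not properly defined, and the named comparison with CRASH, CARG and G8 does not by itself answer the question of discriminant ability. At one AUC of 0.75, moving the cut-off alone takes sensitivity/specificity from 83%/50% to 54%/80%. Those figures rest on an assumed equal-variance binormal model and illustrate the mechanism; they do not predict this trial's results.

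The documents do not support saying that the rule is impossible to apply, that the plan fixes different cut-offs for the different tools, or that a training AUC will be reported as the final performance.

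This is a secondary analysis. The primary AUC analysis and the 160 patients are unaffected. The change should be made because it is cheap and protects the interpretation of a stated objective.

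**What to change.** In Secondary endpoint analysis, or in the analysis plan:

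1. Name the threshold criterion, for example the maximum Youden index or a fixed sensitivity. Derive the cut-off in the training cohort and lock it before the validation data are examined.
2. In the 60 validation patients, compare the continuous linear predictor with the CRASH, CARG and G8 scores by paired AUC difference with a 95% CI (DeLong or bootstrap).
3. Keep sensitivity and specificity as a supplement, at a matched operating point or at published cut-offs stated in advance.
4. Label any training-cohort AUC with a Hanley interval as apparent, and report the validation AUC as the model's performance.

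The cost is wording only: the same patients, the same data and standard software. The drawback is precision. With 60 patients the half-width of a single AUC of 0.75 is about 0.12, and the paired differences may be no tighter unless the scores are well correlated. The text should therefore say that the comparison with published tools is exploratory.

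### As the text is ordered, the toxicity profile's AUC and Hanley 95% CI come from the 100 training patients who built the profile, so the AUC is optimistic and its interval under-covers

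*Protocol article*

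**What the plan says.** The Objectives of the study section makes the profile a secondary objective: "a toxicity risk profile will be studied by using combined scores including parameters of body composition and a geriatric assessment", to be compared with CRASH, CARG and G8.

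Secondary endpoint analysis divides the patients by order of recruitment into "a training cohort (first 100 patients recruited) and a validation cohort (last 60 patients recruited". The steps then run in this order:

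1. An elastic net logistic model is fitted in the training cohort, with mixing parameter 0.5 and lambda chosen by 10-fold cross-validation.
2. Bootstrap selection stability (BSS) is computed: "Only parameters with high BSS will be selected in the final model".
3. A classifier is built from the linear predictor.
4. The profile is dichotomised "using the area under the ROC curve and will be estimated with corresponding 95% confidence interval (Hanley method".
5. "Risk group will be then applied on the validation cohort".
6. Sensitivity and specificity of the risk group are evaluated and compared with the published tools.

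No AUC or interval is named after step 5, and no correction for optimism is named at any step. The cross-validation serves to choose lambda, and the bootstrap serves to measure selection stability.

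**The concern.** The Hanley standard error describes sampling variation in the AUC of a score that was settled without reference to the outcomes being analysed. That holds for ALM in the primary analysis. It does not hold for a profile whose parameters, weights and cut-off were all chosen to separate toxicity from no toxicity in these same 100 patients. The apparent AUC is then too high on average, and the interval around it has no term for the search.

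At stake is how the profile is described. A profile made of noise could be reported with a lower limit above 0.5, and a modest one could appear to reach the 0.75 used for planning. The article hopes that the results will improve predictive models and treatment decisions, so an inflated AUC would matter to readers.

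**Working it through.** **Inputs from the Protocol article.** Training 100 and validation 60; toxicity rate 50%, so about 50/50 and 30/30 events and non-events; mixing parameter 0.5; lambda by 10-fold cross-validation; two-sided 95% Hanley interval.

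**Inputs that the article does not give (assumed).** Number of candidate parameters, their correlations, the BSS cut (0.5 to 0.9 tried), whether lambda is re-tuned in each bootstrap, and whether the selected parameters are refitted without penalty.

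**Step 1: reproduce the plan's own figure.** The sample size section states "Supposing a toxicity rate of 50%, 160 patients were required to estimate a 95% confidence interval"; its planning value is 0.75 and its target half-width 7.5 points. The Hanley-McNeil variance is

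Var(A) = [A(1−A) + (n1−1)(a−A²) + (n0−1)(b−A²)] / (n1·n0), with a = A/(2−A) and b = 2A²/(1+A).

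At A = 0.75: A(1−A) = 0.1875, a−A² = 0.0375, b−A² = 0.0804.

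- 80/80: (0.1875 + 79×0.0375 + 79×0.0804)/6400 = 0.001484; SE 0.0385; half-width 1.96×0.0385 = 0.0755.

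This agrees with the stated ±7.5 points to rounding. The smallest even total that reaches 0.075 or less is 164, against 160 stated.

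**Step 2: the same formula in the two cohorts, A = 0.75.**

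- 50/50: (0.1875 + 49×0.0375 + 49×0.0804)/2500 = 0.002385; SE 0.0488; half-width 0.096.
- 30/30: (0.1875 + 29×0.0375 + 29×0.0804)/900 = 0.00401; SE 0.0633; half-width 0.124.

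With 50/50, the lower limit passes 0.5 once the AUC reaches about 0.611 (0.611 gives 0.501; 0.610 gives just under 0.500).

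**Step 3: the described procedure when nothing predicts toxicity.** Elastic net, cross-validated lambda held fixed across bootstraps, BSS selection, logistic refit, Hanley interval on the training AUC; 600 simulated trials per setting. A trial that selects nothing counts as no false signal. The table gives the share of all trials whose training interval excludes 0.5.

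| BSS cut | 18 candidates | 30 candidates | Second set: 10-30 candidates |
|---|---|---|---|
| 0.5 | 42% | 50% | 44-60% |
| 0.7 | 31% | 39% | 31-40% |
| 0.8 | 25% | 31% | 27-33% |
| 0.9 | 14% | 18% | 17-22% |

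The first two columns assume correlation 0.6 within body composition and 0.2 elsewhere, and count intervals wholly above 0.5 (nominal 2.5%). The last column assumes correlation 0 or 0.3 and counts exclusion on either side (nominal 5%). A further check gave about 13-47%. Leaving out the unpenalised refit changed nothing at cuts of 0.7 to 0.9, and gave 38-40% instead of 44-47% at 0.5.

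In the second set, the mean training AUC of noise models was 0.64 to 0.72 against a true 0.50, already beyond the 0.611 of step 2. Re-tuning lambda in each bootstrap raised the rates to 42-94% of trials (20 candidates, 100 trials).

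**Step 4: coverage with some real signal.** With three true predictors (log-odds 0.4 per SD, assumed) among 30 candidates, the mean training AUC was 0.73-0.79 against a true 0.60-0.61. The nominal 95% interval covered the true value in 18-33% of trials (30-48% with 18 candidates).

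**Step 5: the same null models in the 60 held-out patients (second set).** Mean AUC 0.49 to 0.51. With lambda fixed, the Hanley interval excluded 0.5, on either side, in 1-6% of all trials and about 5-10% of trials that produced a model.

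**The case against.** The strongest reply is that the text does not firmly commit to this. The sentence carrying the interval is garbled: its grammatical subject is the risk group, and it names no cohort. The section opens by saying that secondary objectives follow methodology similar to the primary endpoint, which is an AUC, and 60 patients are set aside for temporal validation. An AUC in those patients is compatible with this, and a condensed article need not list every validation measure.

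Part of that stands. The training placement is a reading from sentence order and from the measures named, and nothing rules out a validation AUC. But the general opening line does not say which patients supply the profile's AUC. The specific paragraph puts the AUC and interval before the move to the validation cohort, so an analyst following the written order would produce the optimistic figure.

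The second reply is that the plan attaches no test or claim to the profile AUC exceeding 0.5. That is correct: 0.5 serves here only as a yardstick for the interval's behaviour. The stated evaluation is sensitivity and specificity after the risk group is carried to the held-out patients, where a noise profile would show a sum near 1. That safeguard is real, though it does not repair the AUC or its interval.

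The third reply is that the rates depend on undocumented inputs. This also stands: a strict reading of high BSS favours the lower rows of the table, and the article names only body composition and geriatric parameters before an ellipsis.

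**Conclusion.** The concern holds in limited form. Followed in the order written, the one AUC with a Hanley interval named for the toxicity profile is biased upward and its interval under-covers. With no true predictor, fixed lambda and 18 to 30 assumed candidates, roughly 13-50% of trials would show an interval wholly above 0.5, against 2.5% nominal. The direction was the same in every setting tried; the exact rate cannot be fixed from the article.

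Three stronger readings are not supported:

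- A reader might infer that the profile is left unvalidated. It is not, because the frozen risk group is checked in 60 later patients.
- A reader might infer that the trial would declare a noise profile successful at these rates. The plan sets no such decision rule.
- A reader might infer that the main result is compromised. The primary AUC concerns one marker named in advance, with no fitting, and is unaffected.

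This should be corrected, but it is confined to one statistic of a secondary, model-building objective.

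**What to change.** In Secondary endpoint analysis, replace the end of the model-building paragraph with wording such as: *The linear predictor and the cut-off are frozen in the training cohort. The AUC of the frozen linear predictor, with its Hanley 95% CI, is estimated in the validation cohort, together with the sensitivity and specificity of the frozen risk group with binomial CIs.*

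Any training-cohort AUC should be labelled as apparent, or reported after optimism correction by repeating the whole procedure (lambda by cross-validation, BSS selection, model fit, cut-off) in each bootstrap resample. In neither case should a Hanley interval be attached to it.

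This needs a few lines of text and no further patients or data. The downside is a lower reported AUC and a wider interval: at an AUC of 0.75, about ±0.124 with 30/30 in validation against ±0.096 with 50/50 in training. The narrower interval is not valid for a score built on the same patients.
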